**Fig. 1 Fig1:**
[figure not shown]
Time schedule and flow of participants

From January 2012 to December 2013, 145 patients at Nanfang Hospital met the inclusion criteria. Based on our experiences during our single-incision laparoscopic appendectomy study, we expect a recruitment rate of 90 to 100 % [19]. No provisions or financial compensation will be offered as recruitment strategies. We expect to recruit 198 patients within 36 months, and the trial is designed to proceed for 96 months.

### Interventions

Surgery will be performed by investigators with ≥ 100 successful laparoscopic colorectal resections and ≥ 10 transumbilical SILS plus one colorectal resections.

#### Experimental intervention

After general anesthesia, the patient will be placed in a lithotomy position on the table. The positions of the surgeon, assistant, and camera operator are depicted in Fig. 2a.

**Fig. 2 Fig2:**
[figure not shown]
Operative position and single-incision multichannel device. **a** The patient is placed in a lithotomy position. The surgeon stands at the patient’s right side with the first assistant at the left side, while the camera operator stands beside the patient’s right shoulder with the monitor placed beside the patient’s left leg. **b** The homemade multichannel device comprises a soft tissue retractor and a surgical glove

An initial 5-cm periumbilical transverse incision will be made. Then, the homemade multichannel device, comprising a soft tissue retractor and a surgical glove, will be placed at the umbilical incision (Fig. 2b). Two 12-mm trocars and one 5-mm trocar will be inserted through the glove fingers as the observation port for a 10-mm 30° laparoscope, the surgeon’s nondominant operation channel, and the assistant’s operation channel, respectively. A pneumoperitoneum of 12-13 mmHg will be established and maintained. One 12-mm trocar will be placed in the right lower quadrant under laparoscopic view as the surgeon’s dominant operation channel (Fig. 3a,b).

**Fig. 3 Fig3:**
[figure not shown]
Trocar positions and surgical procedure for the experimental intervention group. **a**, **b** Trocars and instrument positions for single incision plus one port laparoscopic surgery (SILS plus one). **c** Ligation of the inferior mesenteric artery and vein. **d** The distal rectum is dissected by inserting a linear stapling device through the surgeon’s dominant operation channel

After the abdomen is explored with the laparoscope, the patient will be placed in the Trendelenburg position with the left side elevated 20 to 30°. High ligation of the inferior mesenteric artery approximately 4 cm above the abdominal aortic bifurcation will be performed with a clip for D3 lymphadenectomy (Fig. 3c). Subsequently, the inferior mesenteric vein will be ligated near the duodenojejunal peritoneal fold (Fig. 3c). Then, the medial-to-lateral dissection will be performed. The distal rectum will be dissected by inserting a linear stapling device through the surgeon’s dominant operation channel (Fig. 3d). The surgical specimens will be removed through the umbilical incision under the soft tissue retractor and dissected extracorporeally. Intracorporeal end-to-end anastomosis will be performed using a circular stapler inserted through the anus and tested with air insufflation. A drainage tube will be placed in the pelvic cavity through the surgeon’s dominant operation channel. The fascia and the skin will be reapproximated with simple interrupted absorbable and nonabsorbable sutures, respectively. Then, the incision length will be measured, and the wound will be dressed. Additional movie files show the operation procedure in more detail (see Additional file 1).

#### Control intervention

After general anesthesia, the position of the patient, the surgeon, the assistant and the camera operator will be the same as described for the experimental group (Fig. 2a).

A periumbilical incision for a 12-mm trocar will be made as the observation port for a 10-mm 30° laparoscope. After a 12- to 13-mmHg carbon dioxide pneumoperitoneum is created, additional transabdominal trocars will be placed under laparoscopic view: one 12-mm trocar in the right lower quadrant as the surgeon’s dominant operation channel, one 5-mm trocar in the left quadrant as the assistant’s nondominant operation channel, and two 5-mm trocars in the right and left upper quadrants as the surgeon’s nondominant and the assistant’s dominant operation channel, respectively (Fig. 4a,b).

**Fig. 4 Fig4:**
[figure not shown]
Trocar positions and surgical procedure for the control intervention group. **a**, **b** Trocars and instrument positions for conventional laparoscopic surgery (CLS). **c** Ligation of the inferior mesenteric artery and vein. **d** The distal rectum is dissected by inserting a linear stapling device through the surgeon’s dominant operation channel

After laparoscopic exploration of the abdomen, the surgical procedure will be performed in the same manner described for the experimental group (Fig. 4c,d). After distal rectal colon dissection, an extension incision will be performed, and the rectosigmoid colon will be extracted under a soft tissue retractor and dissected extracorporeally. The procedure that follows will be the same as that described for the experimental group:Mobilization of the splenic flexure will not be performed routinely except in cases of a lack of redundancy of the sigmoid colon [14, 20].In the CLS group, the length and the location of the extension incision will be determined by the surgeon.Adding ports or converting to open surgery will be allowed at the surgeon’s discretion if technical difficulties, the patient’s safety, simultaneous surgery, or unexpected conditions requiring conversion.Only standard straight laparoscopic instruments will be used for the operation.A temporary protective loop ileostomy will be allowed for high-risk patients, such as those taking steroid medication, those with an abscess discovered during surgery, or those with a poor nutritional state [21], at the surgeon’s discretion.The operation procedures for both intervention groups will be digitally recorded and left unedited.Immediately after the operation, an investigator will check the macroscopic quality of the complete mesocolic excision [22] (Fig. 5a) and measure the length of the proximal and distal dissection margins (Fig. 5b) and the tumor diameter (Fig. 5c).

**Fig. 5 Fig5:**
[figure not shown]
Specimen measurement. **a** Macroscopic quality of the complete mesocolic excision. **b** Length of the proximal and distal dissection margins. **c** Tumor diameter

### Perioperative management, discharge, and follow-up

Nutritional support will be performed according to Nutritional Risk Screening 2002 [23] and ERAS Society recommendations [24]. Polyethylene glycol electrolyte solution (2.5 L) will be administered the day before surgery for bowel preparation. A single short dose of prophylactic antibiotics (second-generation cephalosporins) will be given intravenously 30 minutes before surgery [24]. Systemic prophylactic antibiotics (second-generation cephalosporins) will also be given intravenously within 72 hours postoperatively. Nasogastric tubes will not be routinely used [24]. Postoperative patient-controlled opioid-based intravenous analgesia will be routinely administered directly after surgery in the recovery room and discontinued on postoperative day (POD) 2 [25]. Additional analgesics will be allowed in cases of breakthrough pain as recommended by the World Health Organization Analgesic Ladder and at the discretion of the treating ward physician [26]. The patient’s urinary catheter will be removed on POD 3. After the first spontaneous voiding, a bladder ultrasound will be performed to measure the post-voiding residual urine. If the patient has symptoms of urinary retention or is unable to pass urine spontaneously 6 hours after catheter removal, a catheter will be reinserted for at least 24 hours [27]. The drain will be removed at the surgeon’s discretion and based on the amount of drainage and the properties of the drained fluid. Participants will be discharged once they are able to tolerate a soft diet and ambulate independently (defined as being able to walk a predefined distance or go to the bathroom independently [28]).

Postoperative adjuvant chemotherapy will be performed according to the NCCN guideline [29, 30] at the surgeon’s discretion and if the participant is willing. Each participant will be followed up at 1 and 3 months after surgery, then every 3 months for the first 2 years and every 6 months for the next 3 years. Quality of life will be measured with the European Organization for Research and Treatment of Cancer (EORTC) Quality of Life Questionnaire-Core 30 (QLQ-C30) [31], the EORTC Quality of Life Questionnaire-Colorectal 29(QLQ-CR29) [32], and the International Prostate Symptom Score (IPSS) [33] preoperatively and 1 month, 3 months, and 6 months postoperatively. The participants will be evaluated for tumor recurrence using the following methods: physical examination, carcinoembryonic antigen (CEA), carbohydrate antigen 72-4 (CA 72-4), and carbohydrate antigen 19-9 (CA 19-9). Chest radiographs will be obtained every three months for the first 2 years and then every 6 months for the next 3 years. Liver ultrasonography will be performed for the first time at the third postoperative month, then every 6 months for the first 2 years and annually for the next 3 years. Colonoscopy or EUS and abdominal and pelvic CT scans will be performed every 6 months for the first 2 years and then annually for the next 3 years. If the participant fails to return for follow-up visits, he or she will be contacted by phone or email to complete the follow-up data.

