### Recruitment and trial timeline

After being screened for inclusion and exclusion criteria, the potential participants will be verbally introduced to the study by an investigator. A signed written informed consent will be obtained from each patient before his or her inclusion in the study. A copy of the signed consent will be given to the participant, and the original consent will be kept in the hospital. Surgery will be performed within 7 days of patient enrollment or, if it is not, the reason will be recorded in the case report form (CRF). After enrollment, the baseline demographic and clinical characteristics of the participant will be measured preoperatively (Table 2), and any participants who meet the withdrawal criteria (Table 1) will be withdrawn from the trial. The flow of participants and time schedule are presented in Fig. 1.

**Table 2 Tab2:** Preoperative and postoperative outcome parameters and schedule of study visits and follow-up

Measures	Preoperative	Daily in-hospital study visits							Follow-up														
		POD 0^b^	POD 1	POD 2	POD 3	POD 4	POD 5	POD ≥6	M1	M3	M6	M9	M12	M15	M18	M21	M24	M30	M36	M42	M48	M54	M60
Inflammatory parameters (WBC, NE %, CRP, IL-6, TNF-α)	X^a^	X^c^	X^c^			X^c^																	
VAS score			X	X	X		X																
Short-term recovery^d^			X	X	X	X	X	X															
Post-voiding residual urine	X^a^				X																		
EORTC QLQ-C30	X^a^								X	X	X												
EORTC QLQ-CR29	X^a^								X	X	X												
IPSS	X^a^								X	X	X												
BIQ									X	X	X												
Abdominal incision photograph		X							X	X	X												
Physical examination	X^a^								X	X	X	X	X	X	X	X	X	X	X	X	X	X	X
CEA, CA72-4, CA19-9	X									X	X	X	X	X	X	X	X	X	X	X	X	X	X
Chest radiography	X									X	X	X	X	X	X	X	X	X	X	X	X	X	X
Liver ultrasonography										X		X		X		X		X		X		X	
Abdominal and pelvic CT scan	X										X		X		X		X		X		X		X
Colonoscopy or EUS	X										X		X		X		X		X		X		X
Adverse event		X	X	X	X	X	X	X	X	X	X	X	X	X	X	X	X	X	X	X	X	X	X

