#### Secondary endpoints

Secondary endpoints will be measured intraoperatively, at daily study visits, and at 1, 3, 6, 36, and 60 months postoperatively. Operative outcomes include operation time, estimated blood loss during operation, and incision length. Pathological outcomes compromise tumor size, length of proximal and distal resection margins, and number of harvested lymph nodes and will be determined postoperatively by pathological examination. Postoperative inflammation and immune response (white blood cells [WBC], neutrophil percentage [NE %], C-reactive protein [CRP], interleukin-6 [IL-6], and tumor necrosis factor-α [TNF-α]) will be measured at 4 hours, 24 hours, and 96 hours postoperatively. Postoperative recovery (time to first ambulation, flatus, liquid diet, soft diet and duration of hospital stay) will be measured daily in-hospital and determined using participant self-report. Pain intensity will be measured using a horizontal visual analogue scale (VAS; a 0 to 10 cm scale with 0 at the left edge representing no wound pain, and 10 at the right edge representing wound pain as bad as it could possibly be) [37] at rest on POD 1, 2, 3, and 5. Additional postoperative analgesic use will be recorded in the CRF. Body image and cosmesis will be measured using the Body Image Questionnaire (BIQ) [38] at 1, 3, and 6 months postoperatively. The 3-year disease-free survival (DFS) and 5-year overall survival (OS) will be measured at 36 and 60 months postoperatively. Confirmation of recurrence will require either the detection of radiologically apparent lesions that increase in size over time or a pathology evaluation. The DFS will be calculated from the time of randomization to the time of either local or distant progression or death (from any cause and in the absence of evidence of recurrence) in participants who have undergone curative surgery. The OS will be calculated from the time of randomization to the time of death from any cause. All measurements and time points are listed in Table 2.

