#### Statistical analysis

The statistical analysis will be performed using SPSS version 13.0 (SPSS, Inc., Chicago, IL, USA). A two-sided p < 0.05 will be considered significant. Descriptive statistics will be used for baseline characteristics. For categorical variables, including the primary outcome, a χ^2^ test or Fisher’s exact test will be applied. For continuous variables, Student’s t test or the Mann-Whitney U-test will be applied. Kaplan-Meier curves and the log-rank test will be used to analyze the OS and DFS differences between the two groups. We do not plan to perform interim analyses. Missing values will not be imputed. Any outcomes of interest analysis will be performed based on the intention-to-treat population and per-protocol population (PPP), and a standard sensitivity analysis will be performed based on the PPP.

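### Patients who cannot void on POD 3 have no scheduled residual-urine value and leave that comparison because of the outcome being measured (minor)

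*Protocol article*

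**What the plan says.** Under Perioperative management, discharge, and follow-up, the protocol article fixes the day of catheter removal: "The patient’s urinary catheter will be removed on POD 3". The measurement follows: "After the first spontaneous voiding, a bladder ultrasound will be performed to measure the post-voiding residual urine". The next sentence covers patients with symptoms of retention and those "unable to pass urine spontaneously 6 hours after catheter removal, a catheter will be reinserted for at least 24 hours".

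Table 2 (Recruitment and trial timeline) is titled "Preoperative and postoperative outcome parameters and schedule of study visits and follow-up". Its row "Post-voiding residual urine" has two marks, one preoperative and one on POD 3. Nothing is marked on POD 4, POD 5, POD 6 or later, or at any follow-up visit. The Secondary endpoints section presents the table as complete: "All measurements and time points are listed in Table 2". That section does not itself name residual urine.

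The Statistical analysis section adds two general rules: "For continuous variables, Student’s t test or the Mann-Whitney U-test will be applied" and "Missing values will not be imputed".

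**The concern.** Each rule is ordinary alone; the combination causes the difficulty. Measurement depends on voiding, there is one postoperative time point, and missing values stay missing. The value is therefore absent in the patients whose bladder function is worst, and absent for that reason. A comparison of the remaining patients is made in a subgroup selected after randomisation by the outcome.

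At stake is the reading of one recorded measure. If one operation produced more retention than the other, residual urine would understate the difference. If the arms differed only in the proportion unable to void, residual urine would show no difference at all.

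**Working it through.** **What follows from the text.** No stated figure is in question: the article gives no retention rate, no mean or SD of residual urine, and no power for this measure.

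1. The catheter is removed on POD 3, and the scan needs a spontaneous void.
2. A patient with no void by 6 hours is catheterised again for at least 24 hours, which runs past POD 3. No POD 3 post-void value can exist for that patient.
3. Table 2 schedules no later scan. The sentence on the scan names no day, so it could be read to call for one after the second catheter is removed. That value would be taken at least 24 hours after the others, once the patient can void, and would describe the recovered state.
4. With no imputation, the patient is absent from the POD 3 comparison (reading A) or enters with a post-recovery value (reading B). On neither reading does the POD 3 failure to void count in the residual-urine data.

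**Direction and possible size under reading A. All inputs below are assumptions.**

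*Threshold model.* Latent residual urine is normal with SD 1 (on a log scale, say), and a patient cannot void above a threshold common to both arms. Retention r corresponds to a threshold z(r) SDs above that arm's mean. The true shift is z(r of the better arm) − z(r of the worse arm). Among patients with a value, each arm's mean falls by φ(z)/(1 − r).

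- 10 % versus 5 %: z = 1.282 and 1.645, so the true shift is 1.645 − 1.282 = 0.36. The worse arm is seen at 0.363 − 0.1755/0.90 = 0.168 and the better arm at 0 − 0.1031/0.95 = −0.109. Observed shift: 0.168 + 0.109 = 0.28.
- 15 % versus 5 %: z = 1.036 and 1.645, so the true shift is 0.61. The worse arm is seen at 0.608 − 0.2332/0.85 = 0.334 and the better arm at −0.109. Observed shift: 0.44.
- 10 % in both arms with equal function: true shift 0, observed shift 0.

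Simulated Mann-Whitney rejection rates (two-sided 5 %, 99 per arm, 4,000 trials per case):

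| Retention | Patients with a value only | Non-voiders ranked worst |
|---|---|---|
| 10 % vs 5 % | about 56 % | about 70 % |
| 15 % vs 5 % | about 92 % | about 98 to 99 % |
| 10 % vs 10 % (no difference) | about 5 % | about 5 % |

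Ranking non-voiders worst recovers power and does not inflate the type I error.

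*The same mechanism in mL.* Take log-normal residual urine with log-SD 0.9, medians of 40 and 60 mL, and inability to void above a cut-off of 150 to 300 mL. The true mean difference is (60 − 40) × exp(0.9²/2) = 20 × 1.499 = 30.0 mL. Among patients with a value it is 12.0 mL (cut-off 150) to 20.7 mL (cut-off 300). The sign did not reverse in any case tried.

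*Limiting case.* Voiders are identical in both arms (mean 50 mL), retention is 10 % versus 5 %, and patients in retention are given 300 to 500 mL. Over all patients the difference is 0.05 × (300 − 50) = 12.5 mL to 0.05 × (500 − 50) = 22.5 mL. The observed difference is 0.

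**The case against.** **Not a stated endpoint.** The abstract, the primary endpoint and the secondary endpoints omit residual urine, and no hypothesis concerns bladder function. Its standing comes from Table 2, which also lists surveillance tests. This stands and keeps the point minor. Table 2 does, however, call its contents outcome parameters, gives this one a baseline and a postoperative time point, and is said to list all measurements.

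**The scan could come later.** The sentence on the scan gives no day, so a reader who infers that these patients can never have a value goes beyond the documents. A later value, though, comes after recovery and lies outside the Table 2 schedule, so the problem changes form without going away.

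**Not every patient in retention is lost.** The reinsertion rule also covers patients with symptoms, some of whom may already have voided and been scanned. This stands: the gap concerns those with no spontaneous void.

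**Retention has other routes into the data.** Adverse events are recorded on every hospital day, 30-day morbidity is the primary endpoint, and the IPSS is collected at 1, 3 and 6 months. These can carry a retention event, although the article names retention in neither the adverse-event nor the morbidity text, and the IPSS starts too late for transient retention. None of them corrects the residual-urine comparison.

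**This is detail for an analysis plan.** Partly so. The article has nevertheless already fixed the trigger, the single time point and the no-imputation rule, and it is these that combine badly.

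**The harm is conditional.** It might be inferred that the arm with worse bladder function will look better than it is. The documents do not support that as a statement of fact: it requires retention to differ by arm, no rates are given, and after access the operation is meant to be done the same way in both groups.

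**Conclusion.** The point holds as a minor one. Under the stated rules, patients unable to void on POD 3 either drop out of the residual-urine comparison or enter it with a post-recovery value. The loss is caused by the outcome being measured.

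If retention differs by arm, the difference is shrunk. In the threshold model about a quarter of it is lost (0.36 to 0.28 SD, 0.61 to 0.44 SD), and all of it is lost if the arms differ only in complete retention. These sizes rest wholly on assumed retention rates, distributions and thresholds; the documents fix none of them. There is no between-arm bias when bladder function is equal. Neither the primary endpoint nor the sample size is affected.

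**What to change.** Leave the catheter rule unchanged and make three edits.

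1. Reconcile the perioperative text with Table 2, so that both say the same about when the residual-urine scan is taken and which value counts for a re-catheterised patient.
2. Record re-catheterisation in the CRF, noting whether a spontaneous void came first, and report its proportion by arm beside residual urine.
3. State that residual urine is compared by the Mann-Whitney test, with patients who had no spontaneous void before re-catheterisation on POD 3 sharing the worst rank. Patients who voided and were scanned before reinsertion keep their measured value.

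The cost is a few sentences and one CRF item, which is needed because the article prescribes reinsertion but does not say that it is recorded. No new measurement is required. The downside is that the result is a rank comparison and not a mean difference in mL; the values in patients who voided can still be described in mL by arm.

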### Risk-benefit ratio

The potential benefits of SILS compared with CLS are expected to be fewer trocar-related complications, reduced postoperative pain, faster convalescence, and improved cosmetic results [10–14]. The potential risks of SILS compared with CLS for colorectal cancer treatment are prolonged operation time, increased complications, and uncertain oncological outcomes. However, several retrospective studies have reported that the operation time, complications, pathologic outcomes, and 3- to 5-year DFS and OS for SILS were comparable to those of CLS for colorectal cancer [1, 14, 34, 35].

